## 3. Methods

### 3.1. Overview

Prior to implementing the 3WP intervention, we will refine the components of the implementation strategy (below) by engaging stakeholders at each SNH. We will then use a cluster-randomized stepped-wedge type 2 hybrid effectiveness-implementation design to implement the 3WP and assess its effectiveness in improving the EOL experience for SNH patients and their families. One week prior to intervention roll-out, we will conduct training sessions with ICU nurses that go over 3WP objectives, ways to introduce the 3WP to patients and families, and resources available. We will establish a tailored inventory of items that can be used in wish fulfillment based on prior experience and suggestions from each SNH. A research assistant at each SNH will assist with logistics, support nurses with wish implementation if needed, and collect data. Each SNH ICU (cluster) begins in the control phase and will start 3WP implementation at a randomly assigned time (wedge) (Fig 1). Implementation at each center will be staggered by 2 months. This design is useful in situations where 1) there is evidence of efficacy [23,24,26–30] and there is more potential for the intervention to do good than harm, 2) the traditional experimental randomization may be viewed as inappropriate given the nature of the intervention (a stepped-wedge design would allow all safety-net ICUs to initiate the 3WP), and 3) there are logistical constraints to randomization (3WP is a unit-level intervention and randomization at the patient level will likely result in contamination) [44,45].

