### 3.6. Outcomes and analysis

#### 3.6.1. Patient/family outcomes.

The primary outcome is changes in the Emotional and Spiritual Support factor on the family reported BFS after 3WP implementation. Three BFS-derived measures will be analyzed: Respectful Care and Communication (5 questions, Cronbach α = 0.82), Emotional and Spiritual Support (3 questions, Cronbach α = 0.77), and the BFS-Performance Measure (BFS-PM). The Respectful Care and Communication factor score sums 5 items about staff behavior: (1) listened to concerns; (2) provided medical treatment patient wanted; (3) were kind, caring, and respectful; (4) kept family members informed about patient’s condition and treatment; and (5) attended to personal care needs. The Emotional and Spiritual Support (ESS) factor score sums 3 items about whether staff provided: (1) enough emotional support before death; (2) enough spiritual support; and (3) enough emotional support after death. Based on our prior work [31], we hypothesize that the 3WP will increase the ESS factor score. The BFS-PM, a single item asking for a global rating of EOL care, will be a secondary outcome. Secondary outcomes will also include scores on the HADS (depression and anxiety) and PCL-5 (PTSD) measures.

**Statistical analysis**. We will use an analysis approach that accounts for the stepped-wedge design of this study [66,67]. We will use mixed effects logistic and linear mixed effects models to assess the effect of the intervention on the BFS ESS factor score, BFS-PM, FS-ICU, HADS, and PCL-5. These models adjust for center effect and the confounding effects of time and 3WP implementation. With $Y_{ijt}$ as the quantitative outcome for patient i from center j at time t, the model for patient/family reported outcomes is:

$Y_{ijt}=\mu +\alpha_{j}{\;+\;\beta }_{t}+X_{ijt}\theta +\;Z_{ijt}\varphi +\in_{ijt},$

where μ is the intercept, $\gamma_{i}$ is a random center effect,

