#### 3.6.2. Nurse outcomes.

Secondary outcomes include changes in nurse burnout as assessed by MBI-HSS, which consists of 22 items utilizing 7-point Likert scale responses ranging from 0 (never) to 6 (everyday) on items aimed at measuring the 3 dimensions of burnout [63]. The scores of the items in each MBI dimension will be summed; high scores for emotional exhaustion and depersonalization indicate higher levels of burnout, while high scores for personal accomplishment indicate lower levels of burnout. According to a recent meta-analysis on interventions that reduce clinician burnout [68], we anticipate that the 3WP will reduce the burnout by about 0.3–0.45 in effect size. With 150 nurse evaluations at each time point (60% response rate), we will have >85% power to detect a difference the MBI emotional exhaustion scale. This calculation conservatively assumes 0.5 correlations between before and after survey from the same nurses. We will use linear mixed effects to assess the effect of the 3WP intervention on nursing burnout, with nurses as a random effect, within the stepped-wedge study design. The analysis will control for nurse characteristics (i.e., age, sex, race, ethnicity, and years of experience) as well as the unique nurse identifier.

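### The nurse-burnout model in 3.6.2 omits the ICU, the randomised cluster; if it carries calendar time, as a stepped-wedge analysis implies, stable ICU differences leak into the intervention effect

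*Protocol article*

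**What the plan says.** Section 3.6.2 gives the nurse model in two sentences. The first plans a linear mixed model for the intervention effect on burnout, "with nurses as a random effect, within the stepped-wedge study design". The second lists the adjustment set: "The analysis will control for nurse characteristics (i.e., age, sex, race, ethnicity, and years of experience) as well as the unique nurse identifier". Neither names an ICU or center effect, and neither names a time term.

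Elsewhere in the same article:
- Section 3.1 makes the ICU the randomised unit: "Each SNH ICU (cluster) begins in the control phase". It also says "Implementation at each center will be staggered by 2 months".
- Section 3.6.1 says of the family-outcome models: "These models adjust for center effect and the confounding effects of time and 3WP implementation". Its equation has a random center effect and a time effect, with a linear version of the time trend also planned.
- Section 3.5.2 times the nurse surveys from each ICU's own launch: in the month before training, then 6 and 12 months after implementation.
- Section 3.2 says the three hospitals differ in size, catchment area and patient population.

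**The concern.** A nurse random intercept absorbs ICU differences only in part. In a plain before-after comparison this does no harm, because every ICU contributes both before and after surveys and a constant ICU difference cancels. The stepped-wedge form is different. Surveys follow each ICU's launch, so the first ICU's three surveys all fall 2 months before the second's and 4 months before the third's. Without an ICU term, part of any constant difference between the first and third ICU is read as a trend over calendar time. The model then corrects the before-after contrast for that spurious trend, which biases the intervention estimate. The standard error does not reflect this variation, so intervals are too narrow and a null intervention is declared effective too often.

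**Working it through.** **Inputs from the article.** About 250 nurses in 3 ICUs; 60% response, giving 150 evaluations per time point; within-nurse correlation 0.5; effect size 0.3–0.45; launches at months 0, 2 and 4. The two-sided 5% level is stated for the family outcome and taken to apply here.

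**Assumed, because not given.** The ICU share of burnout variance (0 to 0.10), near-equal ICU sizes (83/83/84), and independent response at each wave.

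**1. The plan's own figure.** Power = Φ(d/SE − 1.96), for a before-after contrast with no cluster or time term, at d = 0.3:
- 150 complete pairs: SE = √(2(1 − 0.5)/150) = 0.0816; power 95.7%.
- 150 per wave, of whom 0.6 × 0.6 × 250 = 90 answer both: SE = √((2/150)(1 − 0.5 × 0.6)) = 0.0966; power 87.4%.
- 90 pairs only: SE = √(1/90) = 0.1054; power 81.2%.

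The stated figure of more than 85% is reproduced by the first two variants. At d = 0.45 every variant exceeds 97%.

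**2. Survey calendar (months from the first launch).**

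| ICU | Before | After | After |
|---|---|---|---|
| First | −1 | 6 | 12 |
| Second | 1 | 8 | 14 |
| Third | 3 | 10 | 16 |

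**3. The leak without sampling noise.** Generalised least squares with correlation 0.5, linear month, no ICU term and no true effect. Suppose the first ICU lies 1 SD above the others.
- Complete response: the fitted slope is wrong by −0.025 SD per month. The mean gap between before and after surveys is (6 + 12)/2 − (−1) = 10 months, so the intervention estimate shifts by 10 × 0.025 = +0.25 SD.
- Independent 60% response: the slope is wrong by −0.037 per month, and the shift is +0.37 SD.

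For the third ICU the shifts are −0.25 and −0.37; for the second they are zero. With ICU fixed effects all of them are zero.

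**4. Type I error.** Null simulations with a nurse random intercept, 60% response and linear month. The range covers two independent sets of runs.

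| ICU variance share (assumed) | Time, no ICU | Time and ICU fixed effects (first set) |
|---|---|---|
| 0 | 5.0–5.4% | 5.2% |
| 0.02 | 7.7–8.0% | 5.6% |
| 0.05 | 10.7% (both) | 5.4% |
| 0.10 | 14.8–17.2% | 5.4% |

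The second set gave 4.5–6.2% with ICU fixed effects. With neither time nor ICU in the model, rejection was 4.6–5.6% in the first set and 5.0–5.8% in the second.

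At share 0.10 without ICU, the estimate's true SD was 0.217 against a mean reported SE of 0.150. This implies rejection of 2Φ(−1.96 × 0.150/0.217) = 2Φ(−1.355) ≈ 17.5%, in line with the simulated 17.2%. With ICU fixed effects the two figures were 0.160 and 0.159.

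**5. Sensitivity, time without ICU.** ICU sizes 125/75/50: 11.4% and 15.2% at shares 0.05 and 0.10. Full response at share 0.05: 10.0%. Within-nurse correlation 0.3 at share 0.05: 14.8%.

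**6. Precision (three waves).**

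| Model | SE (SD units) | Power at d = 0.3 | Power at d = 0.45 |
|---|---|---|---|
| No time term | 0.077 | 97% | >99% |
| Linear time, no ICU | 0.157 | 48% | 82% |
| Linear time and ICU | 0.167 | 44% | 77% |

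Nearly all the loss comes from the time term.

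**The case against.** The strongest reply is that the article never states the faulty model. Section 3.6.2 names neither time nor ICU. Read literally, it is a before-after model with no leak. Read as shorthand for the stepped-wedge analysis of 3.6.1, it has both time and center, and again there is no leak. Inflation needs time to be imported and center left out. A reader might therefore infer that the plan as written inflates type I error outright. The article does not support that, because 3.6.2 states no time term.

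What remains is that 3.6.2 does list its random effect and its covariates, and the cluster is not among them, while its reference to the stepped-wedge design points to a time-adjusted analysis. An analyst who follows that list and adds time arrives at the faulty model. This is more than an omission that a condensed article may leave to a fuller document.

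Other replies:
- The nurse identifier might absorb ICU. As a fixed effect it would (simulated error 4.6–5.8%), but the text makes nurses a random effect.
- The ICU variance is not given, and all three ICUs belong to one county system. This stands: at small shares (0.01–0.02) the error is only about 7–8%.
- ICU effects are not a full cure. This also stands. With ICU-by-survey shocks of SD 0.1 (share 0.05), the error was 15.2% with ICU effects and 19.9% without.
- Every before survey (months −1 to 3) precedes every after survey (month 6 on). With categorical calendar time the effect cannot be estimated, with or without ICU, so identification rests on a parametric trend such as a linear one. True, but no reason to omit the cluster.

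**Conclusion.** The concern holds in conditional form. The nurse model as listed omits the randomised cluster. If it is fitted with linear calendar time, type I error rises from a nominal 5% to about 8%, 11% and 15–17% at assumed ICU variance shares of 0.02, 0.05 and 0.10. It stays near 5% if ICUs do not differ or if no time term is used. ICU fixed effects bring it back to about 5–6%, provided ICU differences are constant over the surveys. Nurse burnout is a secondary outcome, and the primary family analysis, which has a center effect, is not affected. A change to the plan is warranted because the remedy is simple and brings 3.6.2 into line with 3.6.1.

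**What to change.** Add ICU as a three-level fixed effect to the nurse model in 3.6.2, beside the nurse random intercept, and state the time term explicitly, so that any time-adjusted analysis has both terms, as in 3.6.1.

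Given linear time, the ICU term costs two degrees of freedom and raises the SE from about 0.157 to 0.167 SD. If ICUs do not differ it does no harm to the error rate (5.2%).

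Two things should be acknowledged alongside it. First, the linear time term, which the stepped-wedge analysis brings with it, by itself about doubles the SE (0.077 to 0.157). The stated power of more than 85% therefore describes an analysis without time adjustment. Second, the ICU term removes only constant differences between ICUs, not shocks particular to one ICU at one survey.

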#### 3.6.3. Outcomes from semi-structured interviews.

We will follow PCORI methodology standards for qualitative analysis [69] to establish rigor and trustworthiness of semi-structured interviews from family members and nurses. Key methods will include performing purposive sampling of interviewees to ensure diversity, using coders from different backgrounds to increase interpretation reliability, and conducting an audit trail for the coding process. Interviews will be transcribed verbatim in the language in which they were conducted using a standardized transcription protocol [70] and imported to qualitative analytic software (*Atlas.ti* v24) for analysis. The qualitative analysis team will be an interdisciplinary team that will include bilingual Spanish speakers. The team will employ thematic analysis to analyze the data collected. The coding team will inductively develop codes describing participant perceptions and feedback regarding 3WP and will work together to develop consensus regarding a set of codes. To facilitate reliability, a codebook will be developed listing each code name, definition, and positive and negative exemplars [71]. The investigators will subsequently develop themes by examining the codes to identify patterns and relationships in the data. Themes will related to participant perceptions about the 3WP with a focus on the ability of 3WP to personalize care, the effect of 3WP on grieving, and opportunities for improvement. The coding team will share generated themes with the rest of the investigative team. Data will be examined for theoretical saturation of themes (when no new themes can be identified from the data) [72,73].

For nurse interviews, themes regarding how the 3WP affected nurses’ perceptions of how well they can provide high quality EOL care and how the 3WP affected their sense of personal accomplishment, emotional exhaustion, depersonalization, and professional morale will be identified using deductive thematic analysis [49,50]. We will also identify themes related to the feasibility and acceptability of the intervention in SNHs and suggestions for implementation improvement.

#### 3.6.4. Implementation outcomes.

The Reach, Effectiveness, Adoption, Implementation, and Maintenance (RE-AIM) framework will be used to define implementation outcomes (Table 2). *Reach:* Each month, we will obtain lists of deaths in each ICU from the bioinformatics department. This will be the denominator to determine the proportion of eligible patients who received the 3WP. Nurses will be asked to document a 3WP note in the EHR, such that we will be able to record who initiated and implemented the initiative and track the number of clinicians involved at each SNH. *Effectiveness:* The effectiveness of the 3WP in improving the EOL experience for patients/families and nurses will be evaluated by surveys and interviews (above). *Adoption.* We will compare variation in rates of 3WP patient enrollment and proportion of clinician participation across the 3 SNHs. *Implementation.* Nurses’ answers to the 4 questions on fidelity to core functions will be averaged and compared across SNHs. We will also describe categories of wishes, number of wishes, and percent of elicited wishes implemented and by whom. We will present the average cost per patient, and the number and proportion of no-cost wishes. These descriptive statistics will be compared across centers and with historical multi-center data [46]. *Maintenance.* We will trend the descriptive statistics (patients enrolled, clinicians involved, wishes implemented, cost of wishes), by month and by center. After 2.5 years, we will conclude survey collection and remove the research assistant who was available to assist with wish implementation but continue to provide monetary resources to purchase items for patients/families for an additional 12-month period. This period will represent the maintenance period and will also provide an estimation of 3WP cost when there is no on-site research assistant should the site choose to continue the intervention; these data will be provided back to 3WP leaders.

**Table 2 pone.0320843.t002:** Application of the RE-AIM framework to mixed method evaluation of 3WP implementation.

Domain	Existing knowledge gaps in 3WP implementation	Quantitative data	Qualitative data
Reach	Extent to which clinicians are willing to uptake 3WP as ICU initiative in SNHs Extent to which under-served patients and families are willing to accept 3W offering	% of ICU nurses involved in 3WP implementation % of eligible patients who are offered and receive 3WP Characteristics of patients who participated (demographics, insurance, clinical characteristics)	Identify factors influencing 3WP acceptability for families Identify factors influencing 3WP feasibility for nurses
Effectiveness	3WP feasibility and effectiveness has not been evaluated in SNHs Quantitative evidence of improved EOL experiences & clinician burnout Whether patient population SNHs will favorably respond to 3WP Whether 3WP has an effect on family psychological symptoms	Effect of 3WP on family’s perspective of EOL care (BFS) Effect of 3WP on family’s anxiety, depression, and PTSD Effect of 3WP on nurse burnout	Explore effect of 3WP on family’s EOL experience, satisfaction, bereavement, and psychological symptoms Explore effect of 3WP on clinician burnout, agency, stress of work
Adoption	3WP adoption as part of EOL care in SNHs unknown	% of eligible patients who receive 3WP as part of EOL care compared across the three SNHs	Ascertain how 3WP is integrated into workflow at each SNH, perceived benefits and burdens
Implementation	The extent of 3WP implementation fidelity (adherence to core functions) in SNHs is unknown; unclear if fidelity will vary across centers Unknown how categories of wishes, # of wishes/patient, cost compare to prior data	Rankings of fidelity to core functions (nurse surveys) Categories of wishes, # of wishes, when implemented, by whom, and cost/patient	Assessment of the forms (and adaptations) used to achieve core functions via nurse and leadership interviews Assessment of families’ and clinicians’ experience of 3WP
Maintenance	Extent to which 3WP becomes embedded into ongoing EOL care in SNHs is unknown	Variation in 3WP implementation over time Continuation of 3WP beyond the study period that included surveys and research assistant	Obtain clinician’s opinions on what influence 3WP maintenance Explore the factors that influence sustainability after removal of research assistant

### 3.7. Status and timeline

We have engaged stakeholders across the 3 SNH’s in individual or group interviews to refine and tailor the implementation plan (section 3.4). Thirty stakeholders participated: 4 unit directors, 11 charge nurses, 3 nurse educators, 7 physicians, 1 palliative care nurse, and 4 bedside ICU nurses). To obtain initial engagement and provide training (core function #1), stakeholders identified existing unit-specific meetings where 3WP can be promoted and formal training provided when appropriate, such as monthly staff meetings, daily shift change huddles, and multidisciplinary rounds. To facilitate bedside wish elicitation (#2), stakeholders recommended badge buddies and a script for nurses to reference, and informational brochures written in patient-preferred languages. To facilitate wish fulfillment (#2), sites recommended establishing an inventory of items to meet the cultural and spiritual needs of a majority Catholic patient population (rosaries, flameless prayer candles, Bibles). The electronic medical record was determined to be the ideal method for documenting 3WP participation (#3). Unit bulletin boards, health system-wide monthly newsletters, and computer screensavers were identified as spaces to recognize 3WP achievements and sustain unit engagement (#4).

3WP implementation occurred at the first SNH on April 1, 2024 and then staggered by 2 months for the subsequent two SNH’s. After-death surveys were first mailed to families of deceased patients on January 2, 2024 and will continue for 3.5 years (approximately ending in June 1, 2027). Survey data will be analyzed, and we anticipate that the results will be ready in 2028. The first family interview was conducted in August 2024. We anticipate that 30–36 interviews will be completed in two years and qualitative analysis of these interviews will be completed in 2027.

## 4. Discussion

This manuscript describes a protocol to implement and evaluate the 3WP, a low cost, high value palliative care intervention in 3 low-resourced hospitals. The study will be performed across 3 SNHs in the Los Angeles County healthcare system, the second largest municipal health system in the nation, and thus will provide valuable insight for implementing palliative care interventions in culturally diverse populations and safety-net settings. The intervention is low risk and there are minimal safety concerns. As a hybrid effectiveness-implementation study that utilizes mixed methods [74], our study will provide rich perspectives by integrating both quantitative and qualitative evaluations.

Our study is not without limitations. First, neither patients nor clinicians are randomized; however, this study will provide an assessment of effectiveness and implementation under real-world conditions. Participation in a randomized trial would require explicit patient and/or family member consent, which would generate confusion for dying patients and their family members about compassionate end-of-life interventions that are determined by randomization. Delayed and declined engagement would likely decrease the sample size and result in a biased patient sample. Second, because 3WP is an initiative that is dependent on nurses to voluntarily offer to their patients, it is also dependent on staffing radios and how busy the ICU is. SNHs may have more limited time and effort to devote to eliciting and implementing wishes for dying patients, although our prior experience has shown that clinicians value the ability to provide this type of enhanced care to their patients and families [28]. We will perform additionally perform an as-treated analysis, but also iteratively assess the best strategies for overcoming SNH limitations throughout the study. Third, three clusters may seem small, but this is an acceptable number of clusters for the stepped-wedge design [45,75]. Fourth, we are anticipating a survey return rate of approximately 40% from families of deceased patients. Although seemingly low, this is typical of after-death surveys and consistent with our experience and prior studies.[25,60,61,76]

In summary, we anticipate that this study will demonstrate the feasibility of implementing the 3WP in the SNH setting, and SNH patients and families will benefit from the 3WP by receiving improved quality EOL ICU care. Our proposal will provide both effectiveness evidence and implementation insights to guide future dissemination of the 3WP and other palliative care initiatives for critically ill patients in SNHs.

